### Data monitoring

Data are monitored centrally according to a predefined monitoring plan, with queries posted for missing and/or inappropriate data. On-site monitoring is performed according to a risk-based strategy. Safety is descriptively monitored throughout the trial by an independent international data and safety monitoring board (DSMB). The DSMB members are unblinded and independent of the study team. Formal event-driven interim analyses are performed to assess intervention safety (discontinuing statins). The main safety concern is the increased risk of CV events and all-cause death in the experimental arm. Therefore, the primary endpoint is monitored. If there is statistical evidence that the proportion of primary outcome events in the experimental arm is higher than 50% based on predefined cut-off limits, the DSMB will be informed to discuss possible adaptation of inclusion criteria (eg, increase of the minimum age if there is a signal in those under 75 years of age) for safety reasons or, in the worst case, termination of the trial, also for safety reasons. For quality assurance, the sponsor, the ethical committee or an independent trial monitor may visit the research sites for an audit.

### Harms

The follow-up assessment is conducted centrally by a team in each main centre per country (Bern, Leiden, Bordeaux). The assessment of SAEs is handled by the respective central teams in each country, even for patients recruited at local sites. The central teams are responsible for performing causality assessments to determine if the SAE is potentially related to the trial intervention (eg, major CV events and all deaths). This process involves a thorough review of the event in the context of the trial’s parameters. A CEC, comprising experts from diverse specialties, for example, cardiology, neurology, internal medicine and geriatrics, is established to perform blinded outcome adjudication of clinical events identified by the central team as suspected SAEs and to determine which events meet the trial’s definition of the primary outcome. Each suspected CV event and all deaths are independently reviewed by two adjudicators who remain unaware of the participants’ group allocation. In the case of disagreement, one of the adjudicators will provide a detailed explanation for the chosen outcome, which will be reviewed by the other adjudicator. If this leads to consensus, the agreed classification will be adopted. If on discussion, the two adjudicators remain in disagreement, a third adjudicator will independently review the event blinded to the prior adjudication results. The third adjudicator’s assessment will be final. The CEC is blinded to group allocation (information on statins, other LLDs and lipid levels are removed from documents to review to maintain blinding).

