**Trial registration number:**

Clinicaltrials.gov: NCT05178420; BASEC (Swiss Ethics Commission): 2021-01513; FOPH (Swiss national portal): SNCTP000005172; Netherlands Trial Register: NL83907.058.23; France Trial Register: 22.04747.000158– IDRCB 2022-A02481-42.

STRENGTHS AND LIMITATIONS OF THIS STUDYThis study is the largest ongoing trial to assess the safety and potential benefit of statin discontinuation in multimorbid older adults, who are often excluded from major randomised controlled trials.In addition to cardiovascular endpoints, this trial assesses patient-centred outcomes important for older adults, such as quality of life, muscle pain, sarcopenia and falls as secondary endpoints.While outcome adjudication and ascertainment is blinded, the lack of participant and physician blinding may introduce bias in treatment adherence and subjective outcome assessments.We engaged patients in safety monitoring, recruitment strategies and dissemination efforts, which increases the study’s relevance and applicability in real-world settings.

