### Follow-up

Follow-up visits will be conducted at 3 months and 12 months after randomisation, then yearly until end of study with a maximum follow-up of 48 months after randomisation. Study personnel will contact the participant and/or GPs by phone and will review medical records to obtain information from hospitals and GPs about medical events and drug treatments during follow-up. We will collect the dosage and frequency of lipid-lowering agents. For concomitant CV treatments, the drug names will be recorded and if they have been established since baseline or started within any of the follow-up periods. At each yearly follow-up call, we will assess the Girerd Medication Adherence Scale. This approach enables continuous monitoring of intervention adherence throughout the study. Additionally, patients and their GPs will be reminded of the randomisation assignment after each follow-up call and instructed to inform the study personnel of any changes in lipid-lowering treatment. Medication adherence will be further assessed with a lipid-level measurement in 100 patients per group at the 1-year follow-up. Patients are not excluded if they are hospitalised during the follow-up period; all participants remain in the study regardless of hospitalisation. All hospitalisations are recorded within the safety reporting, and those potentially related to a CV event or death are adjudicated to ensure accurate outcome assessment.

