### Blinding

This trial is designed as an open-label study, with blinded outcome ascertainment and adjudication.

Regular telephone calls are made by partially blinded study nurses. Partial blinding means that study personnel initially assess participants’ outcome events over the phone without knowledge of their group assignment. This includes some subjective secondary outcomes, such as muscle pain. Blinding is maintained until the assessment of medication compliance, at which point group allocations become known. The primary outcome is also adjudicated by a blinded clinical event committee (CEC) (see Harms section). Blinding participants and treating physicians was deemed unfeasible for several reasons. First, providing multiple placebo tablets of identical appearance and taste for every statin agent and dosage would be impractical and costly. Second, medication changes to a standard dosing of statins in an older population might lead to increased risks of non-adherence and medication-related adverse events.^52^

Pragmatic studies often avoid placebos intentionally, aiming to assess the difference between an intervention and the best current usual treatment. Most large RCTs on deprescribing do not use placebos.^18 53^

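### Outcome ascertainment is called blinded, but staff blinding is secured only until a participant's first compliance assessment, and the central team's choice of non-fatal events for the committee has no stated blinding

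*Protocol article*

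**What the plan says.** **The claim.** The Blinding section opens with "This trial is designed as an open-label study, with blinded outcome ascertainment and adjudication". The strengths and limitations list repeats it without qualification: "While outcome adjudication and ascertainment is blinded, the lack of participant and physician blinding may introduce bias".

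**The calls.** The Blinding section continues: "Regular telephone calls are made by partially blinded study nurses". Outcome questions come first in a call, and "Blinding is maintained until the assessment of medication compliance, at which point group allocations become known". The Follow-up section sets the schedule: "Follow-up visits will be conducted at 3 months and 12 months after randomisation, then yearly until end of study", to a maximum of 48 months. It adds that patients and GPs are told the allocation again after every call.

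**The route to the committee.** Harms gives follow-up and SAE assessment to a central team in each country. It also says: "The central teams are responsible for performing causality assessments to determine if the SAE is potentially related to the trial intervention". The clinical event committee is then to "perform blinded outcome adjudication of clinical events identified by the central team as suspected SAEs". All deaths are reviewed. Hospitalisations are all recorded, but only "those potentially related to a CV event or death are adjudicated to ensure accurate outcome assessment" (Follow-up). The committee works from files stripped of statin, other lipid-lowering and lipid-level information.

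**Unreported events.** Under Statistical methods, a participant with no time-to-event outcome reported as an SAE is counted as event-free.

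**The concern.** Committee blinding protects the classification of the files that the committee receives. It does not protect the choice of files. If those who choose can know the arm, a non-fatal event may be forwarded more readily in one arm than in the other. An event that is not reported is analysed as no event.

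In a non-inferiority trial this acts directly on the conclusion. Under-referral in the discontinuation arm pushes towards non-inferiority. Over-referral there, for example from worry about stopping a statin, pushes away from it. The intention-to-treat and per-protocol analyses use the same adjudicated events, so requiring both to succeed gives no protection.

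**Working it through.** **1. Is the stated property delivered?**

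| Step | Stated protection | What is not stated |
|---|---|---|
| Event questions, up to the first compliance assessment | Asked before compliance; caller blind | – |
| Event questions at later calls | Same order within the call | Any step that restores blinding, such as a different caller |
| Choice of non-fatal events for the committee | Low threshold (suspected or potentially cardiovascular) | Blinding of those who choose; separation from causality rating |
| Deaths | All reviewed | – |
| Adjudication | Two blinded adjudicators, redacted files | – |

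The last two rows are secure. The second and third do not support an unqualified claim of blinded ascertainment.

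**2. When does staff blinding end?** The article does not say at which call compliance is first assessed. The Girerd adherence scale is scheduled at 0, 12, 24, 36 and 48 months, not at 3. If that scale is the compliance assessment, the event questions at month 12 are still asked blind and exposure starts after month 12. If compliance is also assessed at the 3-month call, exposure starts after month 3.

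**3. The plan's own figures (Sample size).** Control risks are 22% at 12 and 34% at 24 months, so S(12) = 0.78 and S(24) = 0.66. There are 900 participants per arm. The margin is 5% × 24 = 1.2 months, or 5.2 weeks.

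- Monthly hazards: h1 = −ln(0.78)/12 = 0.02071; h2 = −ln(0.66/0.78)/12 = 0.01392.
- Restricted mean event-free time: (1 − 0.78)/h1 + (0.78 − 0.66)/h2 = 10.63 + 8.62 = 19.25 months.
- With 2% dropout a year and 12–48 months of uniform follow-up, the standard error of the difference is 0.366 months. Power is Φ(1.2/0.366 − 1.96), about 90.6%, against the stated 89%. The model is therefore close to the plan's.

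**4. Share of events exposed.** Risk by month 3 is 1 − exp(−3 × 0.02071) = 6%. Exposure after month 3 covers (34 − 6)/34 = 82% of first primary events to 24 months. Exposure after month 12 covers (34 − 22)/34 = 35%. Only the non-fatal part of these is open to selective referral.

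**5. Illustrative shift.** The article gives neither the non-fatal share f nor the unreferred fraction q. I assume f = 15–35% and q = 10% in one arm only, with equal true risk. That arm's hazard is multiplied by (1 − f·q) from time s onwards, and the gain over 19.25 months is converted to weeks (× 30.4375/7).

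Example with s = 12 and f = 35%: the factor is 0.965, so h2 becomes 0.01343. The second-year part is 0.78 × (1 − exp(−12 × 0.01343))/0.01343 = 8.644 months against 8.620. The gain is 0.0245 months, or 0.11 weeks.

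| Exposure starts | f = 15% | f = 35% | Share of 5.2-week margin |
|---|---|---|---|
| After month 12 | 0.05 weeks | 0.11 weeks | 1–2% |
| After month 3 | 0.20 weeks | 0.46 weeks | 4–9% |
| Day 0 | 0.27 weeks | 0.63 weeks | 5–12% |

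The shift is nearly linear in q, so q = 20% about doubles each entry. The day-0 row does not follow from the caller mechanism. It needs biased referral from the start of follow-up, which the article does not show.

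**The case against.** The strongest reply is that the article discloses the limit itself. Just after the claim, the Blinding section calls the nurses partially blinded and says when allocations become known. The Discussion repeats this for the geriatric outcomes and lists the open-label design as a limitation. This stands as far as it goes: nothing is concealed. The unqualified wording in the strengths and limitations list remains, and the disclosure does not cover the referral step.

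There are also real safeguards. Staff review medical records and obtain information from hospitals and GPs, all hospitalisations are recorded, data are monitored centrally, and the threshold for referral is low. The Discussion says that all cardiovascular SAEs are adjudicated. These limit the exposure. They do not remove it, because someone still decides which events are suspected to be cardiovascular.

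A reader might go further and infer three things that the document does not support.

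- *The same person calls again knowing the arm, or the referrer knows it.* Roles are described only at team level. Team size, who makes later calls and what staff can see are not stated.
- *Causality cannot be rated without the allocation, or it gates referral.* The examples in Harms (major cardiovascular events and all deaths) can be read as a rating by type of event. No order of causality rating and referral is given.
- *The interviewer-administered questionnaires are damaged in the same way.* Pain is scored only at 3 months. For quality of life and sarcopenia the participant knows the arm anyway, and the article admits that limitation.

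**Conclusion.** The point holds in limited form. The described process secures staff blinding only until the first compliance assessment, and no blinding is stated for the step that decides which non-fatal events reach the committee. The unqualified claim of blinded ascertainment is therefore not supported by the process described.

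The exposure is confined to non-fatal myocardial infarction and ischaemic stroke. Under the assumed inputs it is small to moderate: 1–2% of the margin if unblinding starts after month 12, 4–9% if after month 3, and up to about 12% only with biased referral from day 0. These figures illustrate scale and are not estimates. The non-fatal share and the unreferred fraction are assumptions, and the direction of any bias is unknown. A reader might infer that the trial is biased towards non-inferiority; the document does not support that. The point is worth correcting because the protection is cheap and the records it needs are already collected.

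**What to change.** **Harms.** Replace referral at the central team's discretion with a fixed, allocation-independent list. Every recorded hospitalisation or SAE whose diagnosis or work-up matches suspected myocardial infarction, stroke or TIA, or revascularisation goes to the committee, whatever the team's opinion and before causality is rated. Apply the same list, before analysis, to hospitalisations already recorded.

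**Blinding section and strengths and limitations list.** Replace the claim of blinded ascertainment with: partially blinded ascertainment (staff blinded until the first compliance assessment) with blinded adjudication. State who refers events and whether they know the allocation.

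**Cost.** A change to the adjudication procedure, one pass through existing records and somewhat more dossiers for the committee. Sample size, margin and analysis do not change. Having later event interviews done by a nurse who has not taken that participant's compliance section is optional; the point does not depend on it.

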### Patient and public involvement

Patients were integrally involved in several stages of developing the core outcome sets. Specifically, semistructured interviews were conducted with older patients and caregivers to identify the most relevant outcomes for this population. Public advertisement, magazines, newspapers, the trial’s website (www.statin-stream.ch) and social media will also allow potentially eligible patients to contact the study sites directly in case they seek to participate. To minimise the burden of the intervention on very old and sick patients, special adaptations were planned. These adaptations included printable versions of the questionnaires and priority lists to reduce the follow-up calls. These measures were based on feedback from the first patients enrolled. For patients with cognitive impairments, a tailored process was defined, which allowed study participation with support from their relatives. Additionally, a patient representative is included in the DSMB to provide a patient perspective on the trial’s safety. The study results will be disseminated to patients through newsletters and press releases.

### Ethics and dissemination

The local ethics committee at each site has approved the study protocol and other documentation concerning the study conduct (Ethics Committees in Switzerland (Kantonale Ethikkommission Bern 2021–01513), France (Comite de Protection des Personnes Est I, 22.04747.000158– IDRCB 2022-A02481-42- 1°HPS) and the Netherlands (Medisch-Ethische Toetsingcommissie Leiden/Den Haag/Delft NL-007060, P23.027)).

Where needed, approval by regulatory authorities has also been obtained before enrolment of the first patient. All participants and their data are handled according to the ethical principles of the Declaration of Helsinki.^64^ This study complies with all applicable standards of the International Council for Harmonisation of Technical Requirements for Pharmaceuticals for Human Use - Good Clinical Practice guideline.^65^ The ethics committees and regulatory authorities receive annual safety reports and will be informed about study stop/end in agreement with local requirements. STREAM embraces an open access policy and strives for complete dissemination of the analysis dataset, clinical results and publications.

## Discussion

As there is limited evidence concerning the benefits of statins in primary prevention among older adults, with potential negative effects such as interactions or side-effects associated with statins,^17^ and only a small RCT at end of life about discontinuing statins,^18^ the STREAM trial will provide robust evidence on these research questions.

The design of the STREAM trial has several strengths. First, in order to increase generalisability, the STREAM trial is designed as a multicentric study and involves direct recruitment of participants in GPs’ offices. Second, the STREAM trial focuses on older adults with multiple chronic conditions and will fill a gap in understanding the benefits and risks of statin therapy in this understudied population.^6^ Lastly, the STREAM trial incorporates a primary outcome composed of hard clinical endpoints—a composite of major CV events and all-cause mortality—alongside secondary patient-centred outcomes such as QOL and muscle function, which provide insights beyond CV outcomes.

While the open-label approach offers advantages such as pragmatism, logistical efficiency and direct implementation of findings into clinical practice, it also poses certain limitations. Participants might cross over into the other study group. To address this, regular monitoring and follow-up will assess if participants adhere to their assigned treatments, and we will remind the treating GP at every follow-up of the participant’s treatment allocation. Statistically, we will perform several predefined PP analyses to address this issue. Second, given the open-label design, co-interventions may occur^63^ and will be monitored and addressed, if important differences between both groups arise, as predefined in the SAP. Third, the open-label design might influence the assessment of geriatric secondary outcomes. These outcomes are therefore assessed in a partially blinded manner to lower the risk of bias. In addition, the detection of outcomes will be primarily patient-reported, which might lead to missing data. Missing data will be mitigated by contacting treating physicians for additional information if the patient is not able to answer all follow-up questions. However, the primary outcomes are composed of hard endpoints and not subject to the placebo effect, thus we expect only limited potential bias. An independ ent adjudication committee composed of clinicians, who are not involved in the inclusion or follow-up of STREAM participants and remain blinded to study group allocation, will assess and adjudicate all CV serious adverse events.

Only one trial is currently examining the discontinuation of statins for primary prevention in patients aged over 75 years.^66^ Our trial will have an extended follow-up period and incorporate more patient-centred secondary outcomes. Another ongoing trial is examining statin continuation versus placebo in older patients; however, this trial is not including multimorbid, frail patients.^67^ The STREAM trial will therefore be able to inform future guidelines on the safety and feasibility of discontinuing statins in older adults with multimorbidity. This could help reduce polypharmacy and potentially inappropriate statin prescription, which is highly prevalent in this patient population.^68^ Reducing inappropriate statin therapy will potentially improve the QOL and minimize the risk of adverse drug reactions.^69 70^

The study’s findings will contribute insights into the management of statin therapy among older adults, potentially informing clinical practice and guiding future research.

### Current status of the STREAM trial

The STREAM-trial started recruitment in November 2021 and is expected to be complete in early 2025. The trial follow-up is expected to be completed in 2026.
